## Abstract

**Background:**

Smoking is the main preventable cause of morbidity and mortality in our region, it being the main causative agent of chronic obstructive pulmonary disease. There still is no consensus on the use of spirometry as a strategy for smoking cessation, given that there is insufficient scientific evidence from high quality studies to recommend the use of this technique.

**Methods/Design:**

This is to be a randomized, multicentre, open-label clinical trial. A total of 444 smokers over 40 years of age will be recruited by 39 general practitioners from 22 health centers. Primary objective of this study is to assess the effectiveness of spirometry together with information regarding the test for smoking cessation after 1 year in smokers over 40 years of age with a more than 10 pack-year history and no previous diagnosis of chronic obstructive pulmonary disease. Groups of 45 patients who smoke will be randomly selected from the lists of the participating doctors. The names will be sent to the corresponding doctors who will contact candidate patients and assess whether they meet the selection criteria. Patients who meet these criteria will be randomly allocated to an intervention or control group. For patients in both groups, a nurse will conduct an interview and perform a spirometry test to measure forced vital capacity. Then, all patients will be referred for an appointment with their doctor for brief anti-smoking intervention, patients from the intervention group additionally being informed about the result of the spirometry test. After 1 year, smoking status will be assessed and, in those who report that they have quit smoking, abstinence will be confirmed by co-oximetry. Data will be analyzed on an intention-to-treat basis using the chi-squared test for outcomes and binary logistic regression if it is considered to be necessary to adjust for confounding variables.

**Discussion:**

Performing a spirometry test and providing information on pulmonary function may increase awareness of the effect of smoking among smokers who are asymptomatic or have few symptoms and make them decide to quit. Specifically, in patients with chronic obstructive pulmonary disease it might increase levels of motivation to quit smoking in early stages of the disease. If this strategy were to be effective, it could be included in the health promotion activities offered in primary care.

**Trial registration:**

ClinicalTrials.gov Identifier: NCT01821885

## Background

Smoking is the main cause of preventable mortality and morbidity in industrialized countries. It is estimated that in Spain, as many as 56,000 people die every year due to smoking [1]. It is one of the main risk factors for vascular and respiratory diseases and a causative agent for chronic obstructive pulmonary disease (COPD), accelerating the physiological worsening of the lung volume in susceptible smokers [2,3]. COPD is a disease with a high prevalence (10.2% in 40- to 80-year-olds) and a high rate of under-diagnosis (72% of those with COPD not having been diagnosed), according to the EPISCAN study [4]. It is the fifth cause of death in Spain and one of the main causes of morbidity, responsible for a profound worsening in quality of life, especially in advanced stages of the disease [5]. The World Health Organization (WHO) predicts that by 2030, COPD will go from 12^th^ to 5^th^ place in the list of most prevalent diseases in the world, and from 6^th^ to 3^rd^ place in terms of mortality [6]. These data justify the Spanish National Health System launching a strategy against COPD in 2009 [7] focused around smoking cessation interventions.

Smoking is the main cause of COPD, being associated with more than 80% of cases. According to a study by Fletcher et al. [2], 15 to 20% of smokers develop COPD, more recent studies [8,9] arguing that the figure may in fact be as high as 50%. After the results of the Lung Health Study [10] in 1994, a randomized clinical trial that demonstrated that an intensive anti-smoking intervention in patients with mild and moderate COPD managed to halt the decline in FEV1, several consensus statements have recommended spirometry testing in smokers to benefit their general health. In 2000, one of the main sponsors of the screening programs for COPD was the American National Lung Health Education Program (NLHEP) [11] who advocated the use of spirometry for COPD screening in all patients with any respiratory signs and in smokers aged over 45 years old. COPD meets some of the criteria proposed by Frame and Carlson [12] to justify a screening program, that is, it is an important health problem with an long initial asymptomatic stage; there is a screening test with high sensitivity and specificity, namely spirometry, which is considered the gold standard for the diagnosis; and there is a treatment that, if administered in the asymptomatic stage, is effective in reducing overall morbidity and mortality, in this case smoking cessation [2].

Any screening test must have a good cost-effectiveness ratio. The cost-effectiveness of spirometry depends on various factors, such as the number of patients that need to be screened to detect one case of COPD or, better, to result in one person stopping smoking. In the Lung Health Study [10], the most significant results were obtained in middle-aged patients (mean age of 48 years), with mild or moderate COPD (mean post-bronchodilator FEV1 of 78%), most of whom did not consider themselves “ill”: patients from the anti-smoking intervention group had a smaller decrease in FEV1, the authors concluding that spirometry is cost-effective since it permits the early detection of COPD and focusing measures on these patients. Other authors [13] concluded that even modest quit rates attributable to spirometry may be cost-effective, although the authors comment that further studies are required to assess the independent role of spirometry in smoking cessation.

Later, in 2005, the American Agency for Healthcare Research and Quality (AHRQ) published a systematic review [14] concluding that the benefits of spirometry for opportunistic screening to detect COPD in smokers and ex-smokers will remain unclear until it is demonstrated that spirometry contributes to increasing the number of patients who quit smoking. This review included seven clinical trials of which only one [15] assessed the independent contribution of spirometry in smokers and, though they found the quit rate was higher among those who underwent spirometry as well as receiving advice (6.5 vs. 5.5% in those who only received advice), the difference was not significant. The authors of this review also indicated the need for further studies to determine the role of spirometry in smoking cessation. Another systematic review, that of the U.S. Preventive Services Task Force (USPTF) published in 2008 [16], a subsequent systematic review [17] and a 2005 Cochrane review, on the efficacy of assessing biomedical risks (among them pulmonary function) as a tool for quitting smoking [18], all concluded that the evidence of a role of spirometry as a motivational tool to encourage smoking cessation is inconclusive, as most studies had a short follow-up period and significant limitations, such as not assessing the independent role of spirometry and insufficiently large sample sizes.

A 2012 updated review of the Cochrane Collaboration [19] found little scientific evidence of an effect on quitting smoking for most biomedical tests. Out of the 15 studies included, only 2 of them detected a significant effect: a trial based on ultrasound of carotid and femoral arteries and another on spirometry combined with information on test results in terms of “lung age” [20] which found a significant improvement in the smoking cessation success rate compared to the control group that did not receive the spirometry test report (RR 2.12; CI 95% 1.24 to 3.62). Nevertheless, this study still did not assess the independent role of spirometry, as testing was used in both the experimental and control groups.

Based on the available evidence, the executive summary of the Global Initiative for Chronic Obstructive Lung Disease (GOLD) published in 2013 [21], the international reference, the guidelines of the Spanish Society of Family and Community Medicine and the Spanish Society of Pulmonology and Thoracic Surgery (semFYC-SEPAR) [22] and the 2012 Spanish guidelines for COPD (GesEPOC) [23] advocate “opportunistic” case finding by spirometry only in smokers with respiratory symptoms. However, there is no consensus on this strategy in the scientific community, some authors questioning the usefulness of COPD screening in asymptomatic smokers due to the weak correlation between these symptoms in smokers and COPD. A cohort study [24], including 3,955 people in the USA recruited between 1980 and 2008, that attempted to assess the association between respiratory symptoms and airflow obstruction, confirmed the under-diagnosis of airway obstruction in smokers and concluded that respiratory symptoms have low sensitivity, specificity, and positive and negative predictive values for diagnosing COPD, given that these symptoms are common in smokers with and without airway obstruction; on this basis, the authors advocate spirometry testing in all smokers older than 40 years of age with a more than 20 pack-year history of smoking with or without respiratory symptoms.

Therefore, given the available evidence and the lack of high quality clinical trials assessing the independent role of spirometry in smoking cessation, and that discovering they have COPD may help people quit smoking, we believe that the study we propose may be useful to clarify various issues. Specifically, if our hypothesis were to be correct and spirometry testing did help people quit smoking, public health authorities would have a basis on which to promote this strategy, as it would have the potential to change lifestyles and thereby prevent highly prevalent medical conditions such as various types of cancer and cardiovascular disorders, as well as COPD. Additionally, if a significantly higher rate of smokers with an early diagnosis of COPD quit smoking than those with no diagnosis of airway obstruction, the demonstrated beneficial effect in terms of reducing morbidity and mortality due to COPD, would in itself justify the screening. If, on the other hand, no significant effect on smoking cessation were detected, there would be no arguments supporting COPD screening by spirometry, and we should probably stop performing spirometry tests for this purpose, thus avoiding an unnecessary use of resources. The protocol we present here aims to provide evidence to address this issue, by attempting to determine whether conducting spirometry testing to screen for COPD and informing individuals about their results is effective in encouraging smoking cessation in smokers older than 40 years of age with a more than 10 pack-year history.

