### Objectives

The primary objective of this study is to assess the effectiveness of spirometry testing together with providing patients with information about their results for smoking cessation after 1 year in people older than 40 years of age with a more than 10 pack-year history who have not been diagnosed with COPD (at the outset of the study). The secondary objectives include comparing the quit rates in patients with a new diagnosis of COPD and those with normal lung function, and comparing the change in daily smoking rate between the intervention and control groups.

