#### *Control group*

The nurse will only interview the patient to collect data on the study variables and make them an appointment with their GP within 10 days. The doctor will just perform the brief anti-smoking intervention in the same standardised way as for the intervention group. These patients will not undergo spirometry during the study period of 1 year.

Nurses selected will have the skills and experience necessary for performing spirometry. After finishing this first phase of the study, two doctors with extensive experience in interpreting spirometry will assessed test results and exclude from further analysis any patients whose results do not comply with the criteria for acceptability and repeatability of the American Thoracic Society/European Respiratory Society (ATS/ERS). The nurses involved will not deliver any intervention for smoking cessation to the participants of either group; they will only conduct the interviews and carry out the spirometry, avoiding making any comments on the test results or any other issues related to the patient’s health or smoking habit.

The research doctors will receive training in the study protocol, including how to deliver the brief anti-smoking intervention and report the results of the spirometry test, and will receive a manual with written instructions, summarized in Table 2. In order to avoid variability attributable to the use of different measurement devices, the same models of spirometer (Datospir 120-C) and carbon monoxide detector (Dräger Pac 7000 CO) will be used for all the measurements.

**Table 2 T2:** Intervention by the doctor – instruction manual (summary)

**Brief anti-smoking intervention**	**Information on the spirometry results**

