## Discussion

The role of primary care in the early diagnosis of COPD is indisputable, as is the need for spirometry testing to diagnose this condition [25]. This technique is currently well established in primary care consultations, the quality of the tests having greatly improved in this level of care [24]. On the other hand, the early diagnosis of COPD by spirometry is still somewhat controversial. Assuming that most of the diagnoses would be mild or moderate COPD, the most important measure to improve morbidity and mortality would be smoking cessation and, as we have noted, very few high quality studies have assessed the independent role of spirometry for achieving this objective[14,16]. Of all the studies identified, only two investigated the independent role of spirometry for smoking cessation and both reached negative conclusions [15,26]. More recently, in 2008, Parkes et al. [20] found that by presenting spirometry results in terms of “lung age” there was a greater decrease in smoking than in a control group who were presented the results in the usual way. Nevertheless, this study does not fully clarify the role of spirometry as testing was performed for both groups. Some previous observational studies [27,28] have found higher quit rates in patients diagnosed with COPD. On the other hand, in order to achieve good results in COPD screening, the increase in quit rates would need go beyond the patients with a new diagnosis of COPD, and extend to smokers in general; this is because if there were higher quit rates in COPD patients without a parallel increase across all the smokers analyzed, the intervention would lose some of its value, since we could assume that the absence of effectiveness were due to the potential reassuring effect for many smokers of discovering that they have “normal” lung function. For this reason, the primary objective of our study is to assess whether performing spirometry and informing patients of the results increases the quit rate in smokers over 40 years of age with a smoking history of more than 10 pack-years, whether they have COPD or not, the secondary objectives being to achieve smoking cessation in those with COPD and decrease the consumption of cigarettes in those who continue to smoke.

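### A higher quit rate in newly diagnosed COPD than in smokers without obstruction cannot by itself justify screening: the contrast is not randomised, and the article elsewhere asks for more

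*Protocol article*

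**What the plan says.** Near its end, the Background of the protocol article sets out how results will be read. After the main hypothesis it adds a further case: "if a significantly higher rate of smokers with an early diagnosis of COPD quit smoking than those with no diagnosis of airway obstruction", the effect on COPD morbidity and mortality "would in itself justify the screening". The next sentence says that if no significant effect on cessation is found, nothing would support COPD screening by spirometry.

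The Objectives list, as a secondary objective, "comparing the quit rates in patients with a new diagnosis of COPD and those with normal lung function". The comparator is slightly different: normal lung function here, absence of obstruction in the Background. The restrictive pattern in Table 1 falls between the two.

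The Discussion takes another line. For screening to succeed, "the increase in quit rates would need go beyond the patients with a new diagnosis of COPD, and extend to smokers in general"; and "without a parallel increase across all the smokers analyzed, the intervention would lose some of its value". The reason it gives is that a normal result may reassure many smokers.

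On who is tested, the Control group section says of controls: "These patients will not undergo spirometry during the study period of 1 year". The abstract says the opposite: "For patients in both groups, a nurse will conduct an interview and perform a spirometry test to measure forced vital capacity".

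**The concern.** The Background sentence ties a conclusion about screening to a comparison that cannot measure what screening does. Under the Control group section every patient in the contrast has been tested, and the groups are formed by lung function. A gap in quit rates can arise in at least three ways:

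- The COPD diagnosis prompts quitting.
- The two groups would have quit at different rates anyway. The Discussion itself cites research linking COPD risk to cumulative smoking, so different smoking histories are expected.
- A normal result lowers quitting among the others. This would be a harm of testing, yet it widens the gap and so counts in favour of screening.

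Only the randomised comparison, in all smokers, captures the net result. At stake is what the trial may conclude if its primary result is null and the COPD contrast is significant. In that case the two adjacent Background sentences give opposite answers.

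**Working it through.** **1. The plan's own figure.** Inputs from Methods/Design: quit rates 5% and 14%, two-sided 5% chi-squared test, 80% power, 1:1 allocation, 25% loss. The mean rate is (0.05 + 0.14)/2 = 0.095.

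n per arm = [1.960 × √(2 × 0.095 × 0.905) + 0.842 × √(0.05 × 0.95 + 0.14 × 0.86)]² / 0.09² = 165.4, so 166. Then 166/0.75 = 221.3, so 222 per arm and 444 in total. The stated figures reproduce, without continuity correction. They size the randomised comparison only.

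**2. Why the gap does not measure the effect of screening.** Let *s* be the COPD share, *p₁* and *p₀* the quit rates with and without COPD in the tested arm, and *c₁* and *c₀* the rates the same kinds of smoker would have without testing.

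- Gap used in the Background: *p₁ − p₀*
- Net effect of testing: *s*(*p₁ − c₁*) + (1 − *s*)(*p₀ − c₀*)

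If controls have no spirometry, *c₁* and *c₀* are not observed. Take *s* = 0.20, *p₁* = 12%, *p₀* = 3% (assumed values):

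- Overall rate in the tested arm: 0.20 × 12% + 0.80 × 3% = 4.8%, against the planned control rate of 5%.
- If *c₁* = *c₀* = 5%: net effect = 0.20 × (+7) + 0.80 × (−2) = 1.4 − 1.6 = −0.2 percentage points. The diagnosis helps, the normal result harms, and nothing is gained overall.
- If *c₁* = 12% and *c₀* = 3%: testing changes nothing in either stratum.

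The gap is 9 points in both cases, so it cannot tell them apart.

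**3. How often the Background condition would be met.** With 166 evaluable patients in the tested arm and a 20% COPD share there are 33 with COPD and 133 without. Probability of a significant COPD excess, uncorrected two-sided 5% chi-squared test, by exact enumeration:

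| Quit rate, COPD vs other | Arm overall | P(significant COPD excess) |
|---|---|---|
| 5% vs 5% | 5.0% | 4% |
| 10% vs 3.75% | 5.0% | 33% |
| 12% vs 3% | 4.8% | 55% |
| 15% vs 2.5% | 5.0% | 76% |

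Holding the arm at 5% overall and varying the COPD share from 10.2% to 30%, simulation gives 21% to 53% when 10% of COPD patients quit, and 47% to 98% when 15% do.

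**4. Sparse data.** Expected quitters in the arm: 166 × 0.05 = 8.3 with no effect, 166 × 0.14 = 23.2 at the planned effect. For 12% vs 3% this means about 4 quitters in each stratum. The table 4/33 vs 4/133 gives p = 0.029 uncorrected, 0.051 by Fisher's exact test and 0.083 with Yates' correction; the smallest expected count is 8 × 33/166 = 1.6. By Fisher's test the 55% becomes about 45%.

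**5. The passages side by side, for a null overall result with a significant COPD gap.**

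| Place | Reading |
|---|---|
| Background, claim | Screening is justified by this alone |
| Background, next sentence | No arguments for screening |
| Discussion | Intervention loses some of its value; the increase should reach all smokers |

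**The case against.** The sentence stands in the Background. Neither the Objectives nor the Statistical analysis section makes the COPD contrast a success criterion, and the primary outcome and sample size rest on the randomised arms. A reader might infer that the trial has a formal second route to a positive result; the document does not go that far. What it has is a published statement of how a listed secondary objective would be interpreted, and that is enough to need correcting.

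The Discussion already explains the reassurance effect and gives it as the reason for a primary objective covering all smokers. Its wording is graded: such an intervention loses some of its value, not all. The Background claim also opens as an addition to the main hypothesis, which might mean it presupposes an overall effect. The words *in itself* make that hard to sustain, and the Discussion still asks for an overall increase that the Background claim omits.

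Three stronger readings are tempting and are not supported:

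- *That the strata are known to differ in age, smoking history and symptoms.* The article supports only smoking history. It reports a weak link between symptoms and COPD, and states no age difference.
- *That failing to fix adjustment covariates is a defect.* These are commonly left to an analysis plan, which is not shown.
- *That the share of smokers who develop COPD, given in the Background, is the share to expect at entry.* It is not: patients already diagnosed are excluded, and the figure concerns developing the disease. The 20% here is an assumption.

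Finally, the statement that strata exist only in the tested arm follows the Control group section, and the abstract disagrees. If both arms were tested, the COPD contrast would still not be randomised.

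**Conclusion.** The point holds and should be corrected. A significant excess of quitters among newly diagnosed COPD patients does not justify screening by itself, because the groups are not randomised and the gap can come from prognosis or from reassurance of the others. The claim is also out of line with the Discussion and with the sentence that follows it.

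The size is illustrative. At a 20% COPD share and about 5% quitting in both arms overall, the condition would be met in roughly 33% to 76% of trials with no net benefit, and in about 55% for 12% vs 3%. These figures rest on assumed stratum rates and COPD share, 166 evaluable patients in the arm and the uncorrected chi-squared test; an exact test lowers them. The logical fault does not depend on them. The randomised primary analysis and its sample size are sound on this point.

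**What to change.** - In the Background, delete the words saying that the COPD result alone would justify screening. State that the screening conclusion rests on the randomised comparison in all smokers, as the Discussion implies.
- Label the COPD-versus-normal comparison as observational and exploratory, and use one comparator throughout (normal function or no obstruction).
- Report the quit rate in each spirometry stratum with its 95% CI, beside the rate in the whole control arm.
- Keep any adjustment to one or two baseline covariates already collected, such as pack-years. About 8 to 23 quitters in the arm will not support more.
- Reconcile the abstract with the Control group section on whether controls have spirometry.

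The cost is wording and one descriptive table from data already planned; no patients or visits are added. The real price is that the sponsor gives up a secondary route to a positive claim.

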A sample of 444 people will be recruited. The sample size calculation was based on assuming a level of significance of 5%, a quit rate after brief anti-smoking intervention only (control group) of 5% [23], an expected quit rate in the experimental group of 14% [20], and a 1:1 ratio of control to experimental subjects. Given these premises, to obtain a power of 80% to detect differences in the test of the null hypothesis Ho: p1 = p2 using a two-tailed chi-squared test for two independent samples, it would be necessary to include 166 experimental units in the reference group and a further 166 in the experimental group, making a total of 332 units for the study. Assuming a loss to follow-up of 25%, it would be necessary to recruit 222 subjects for the reference group and a further 222 for the experimental group, summing to the aforementioned total of 444 subjects for the study. The flow chart for the study is presented in Figure 1.

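### The Background reads a non-significant result as leaving no case for spirometry screening, but the trial is powered only for a 9-point gain, so non-significance cannot support that for smaller gains

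*Protocol article*

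**What the plan says.** Three parts of the protocol article bear on this point.

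- **Background, last paragraph (value of the study).** If "no significant effect on smoking cessation were detected, there would be no arguments supporting COPD screening by spirometry". The sentence goes on to say that testing for this purpose should probably be stopped to save resources. The trigger is the absence of statistical significance. The sentence just before it says that a significantly higher quit rate in smokers newly diagnosed with COPD would by itself justify screening.
- **Background, paragraph on cost-effectiveness.** Other authors are reported as concluding that "even modest quit rates attributable to spirometry may be cost-effective". No figure is given, and those authors are also said to want further studies.
- **Methods/Design, sample size.** The calculation is made "to obtain a power of 80% to detect differences" between a 5% control rate and a 14% intervention rate, "using a two-tailed chi-squared test for two independent samples", with 166 evaluable patients per arm and 222 recruited per arm after allowing for 25% loss.

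The Statistical analysis section plans an intention-to-treat chi-squared comparison, with relative risk, absolute risk reduction and number needed to treat, each with a 95% confidence interval. The article names no smallest worthwhile difference and does not tie the negative conclusion to the interval.

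**The concern.** The sentence treats failure to reject the null hypothesis as evidence that spirometry has nothing to offer. A superiority test sized for a large effect (9 points, relative risk 14/5 = 2.8) can easily be non-significant when a smaller real gain exists. The article has reason to be careful here. It reports that modest gains may be cost-effective, and it reports that reviews found the evidence inconclusive partly because earlier samples were too small. Its own null result is not allowed the same reading. What is at stake is a recommendation to abandon a practice on data that may still be compatible with the effect the trial was designed to find.

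**Working it through.** **Inputs (Methods/Design, sample size):** two-sided 5% level; 80% power; control rate p1 = 0.05; intervention rate p2 = 0.14; 1:1 allocation; 25% loss. From the Background: the lung-age trial's relative risk of 2.12. The 8% and 10% intervention rates below are my assumptions, chosen to show a range.

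**1. Reproduce the stated sample size.** With p̄ = (p1 + p2)/2,

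n = [1.960·√(2p̄(1−p̄)) + 0.8416·√(p1(1−p1) + p2(1−p2))]² / (p2−p1)²

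For 5% against 14%, p̄ = 0.095, so n = (1.960 × 0.4147 + 0.8416 × 0.4098)² / 0.09² = 1.1576² / 0.0081 = 165.4, that is 166 per arm. Then 166 / 0.75 = 221.3, that is 222 per arm and 444 in total. The article's figures match.

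**2. Power at smaller effects.**

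Power = Φ{[(p2−p1)√n − 1.960·√(2p̄(1−p̄))] / √(p1(1−p1) + p2(1−p2))}

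With n = 166:

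- 5% against 8%: (0.3865 − 0.6833) / 0.3480 = −0.853, power 20%.
- 5% against 10%: (0.6442 − 0.7301) / 0.3708 = −0.232, power 41%.
- 5% against 10.6% (5% × 2.12): (0.7215 − 0.7433) / 0.3772 = −0.058, power 48%.

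| Intervention rate (control 5%) | 166 per arm | 222 per arm | 222 per arm, losses counted as smokers |
|---|---|---|---|
| 14% | 80% | 90% | 79% |
| 10.6% (RR 2.12) | 48% | 60% | 47% |
| 10% | 41% | 52% | 40% |
| 8% | 20% | 25% | 19% |

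The last column assumes 25% lost in each arm, so both rates are multiplied by 0.75. Exact binomial enumeration of the uncorrected chi-squared test for the first two columns agrees to within about 2 percentage points. Power reaches 50% at an intervention rate of about 10.8% with 166 per arm, or 9.9% with 222.

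**3. What a non-significant result can leave open.** Take 8/166 (4.8%) against 17/166 (10.2%), an illustrative table. The pooled rate is 25/332 = 0.0753.

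- Difference: 9/166 = 0.0542. Relative risk: 17/8 = 2.1.
- Test: z = 0.0542 / √(0.0753 × 0.9247 × 2/166) = 0.0542 / 0.0290 = 1.87, p = 0.06.
- 95% CI: 0.0542 ± 1.96 × 0.0288, that is -0.2 to +11.1 points.

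The result is not significant, yet the interval contains the 9-point design effect. By contrast, observed rates of 5% and 8% with 166 per arm give -2.3 to +8.3 points. That is also non-significant and does exclude 9 points, but it does not exclude a gain of 3 or 5.

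**4. What the interval can exclude.** With 5% observed in both arms the half-width is 1.96·√(2 × 0.05 × 0.95/n): 4.7 points for n = 166 and 4.1 points for n = 222. A 9-point effect would be excluded. To put the upper limit below 3 points, the intervention arm would have to do worse than control by roughly 4.7 − 3 = 1.7 points (166) or 4.1 − 3 = 1.1 points (222).

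**The case against.** The sentence stands in the Background as rationale and is not an analysis rule. The action is hedged (testing should probably stop), and the Statistical analysis section attaches no decision to a null result and will report intervals. The paragraph also gives a second route to supporting screening, through higher quitting in newly diagnosed COPD. One could further read the sentence as placing the burden of proof on screening: without a demonstrated effect, the case has not been made.

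Part of this stands and limits the point. It does not remove it. The hedge covers the action, not the statement that no arguments would remain. The COPD comparison does not measure the effect of testing against no testing. A burden-of-proof reading would support withholding a recommendation, but the text goes further and suggests stopping on the strength of the null result.

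A reader might infer more than the article supports:

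- *That the trial would miss effects the article itself calls worthwhile.* The remark on modest gains is attributed to other authors, says only that they may be cost-effective, and has no figure.
- *That the sentence gives a wrong recommendation in about 80% or 59% of trials.* Those are the chances of a non-significant test at 8% and 10% with 166 per arm. They become error rates only if 3- and 5-point gains are taken to be worthwhile, which the article does not establish.
- *That the trial usually misses a doubling of the quit rate.* This depends on the number analysed: power is 41% with 166 per arm, 52% with 222, and 40% if losses count as smokers.
- *That the sample size is wrong.* It is right for its stated inputs.

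**Conclusion.** The point holds as one of interpretation. Non-significance in this trial does not support the conclusion that spirometry screening has no case, because the design gives 80% power only for a 9-point gain. At a 5% control rate, power is 20% to 25% for a 3-point gain, 41% to 52% for a 5-point gain and 48% to 60% for a relative risk of 2.12, over 166 to 222 per arm with undiluted rates. A non-significant result can even leave the design effect inside its interval. The figures rest on the article's control rate and test, and on assumed intervention rates of 8% and 10%. The primary test and the sample size are unaffected. Severity: minor to moderate.

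**What to change.** Reword the Background sentence so that a negative conclusion rests on the 95% confidence interval for the risk difference that the Statistical analysis section already plans. For example: *A non-significant difference will be taken as evidence against an effect of a given size only if the upper 95% confidence limit for the difference in quit rates lies below that size; otherwise the trial will be reported as inconclusive for smaller effects.*

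The reference size should be at the least the 9-point design effect. If the investigators want to claim that there is no worthwhile effect, they need a smaller minimum worthwhile difference, justified and fixed before the analyst is unblinded. It cannot be read off the cost-effectiveness remark, because the article gives no figure for it.

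The change needs no extra patients, visits or analyses. Its real cost is in what can be claimed. With a half-width of 4 to 5 points at 5% in both arms, a margin of about 3 points will usually be out of reach, so a null trial will often have to be reported as inconclusive.
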